### Adverse effects

Patients will be interviewed daily during admission and at each visit after discharge regarding the occurrence of any adverse events, including time of onset, duration and severity. At each interview, patients will be assessed for reported bleeding classified by the TIMI bleeding classification scheme [20] as well as the BARC definition [21]. All information regarding adverse events will be to be presented on a case report form. The causal relation to the study drug and the intensity of adverse events will be evaluated by the investigators. Serious adverse events will be reported to the IRB and study sponsor by the principal investigator within 24 hours of being reported by the subjects or the treating physicians.

### Withdrawals

Participants are free to withdraw from trial participation at their own request at any time without giving reasons for their decisions. Additionally, the primary investigator may withdraw study participants if continuation of the trial is deemed to be detrimental to the patient’s well-being. Withdrawals will be documented in the case report form and in the patient’s medical records with active follow-up for ongoing severe adverse events. Distinction will be made between patients who ‘withdraw from the study’ versus ‘withdraw from the treatment’ in order to preserve the ability to analyze endpoints for all participants who underwent randomization, allowing for the later possibility of intention-to-treat inferences.

### Sample size

The sample size calculation is based on the primary outcome and the primary analysis for the intention-to-treat population. The sample size is calculated using the study’s primary objective to detect a 15% difference in PR suppression between reloading with prasugrel and clopidogrel, to a power of 80% to demonstrate difference. On the basis of previous reports we assume the inhibition of PR after a LD of clopidogrel to be approximately 55% of baseline [22]. The assumed inhibition of PR after LD of prasugrel is 70%. This was calculated from studies showing a 30% higher concentration of the active metabolite in patients of East Asian ethnicity [23] and an approximate 90% inhibition of baseline PRU two hours after a prasugrel 30 mg LD was given in healthy Korean people [24]. We expect the difference in PR inhibition will be at least 15% when considering ACS patients. We adjusted the sample size for an estimated follow-up loss rate of 20%, a two-sided level of significance of α = 5%, which determined that 38 patients in each group would be required to detect this difference with a two-sided Student’s *t* test. A total of 76 patients will be randomized and included in the analysis. We predict that 50% of patients will exhibit HPR as determined by VerifyNow (Accumetrics, San Diego, CA, USA) after receiving the clopidogrel LD. A total of 152 patients will be screened and 76 patients will be randomized and included in the analysis, with 38 patients in each group.

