### Intervention and comparator descriptions

Before randomization, 300 mg of aspirin and 600 mg of clopidogrel will be administered as LDs according to the conventional guidelines for ACS [2]. For those who have already been receiving clopidogrel for five days or more, 300 mg of clopidogrel will be administered as a LD. PR will be evaluated before PCI and defined as the time between the arrival of the patient at the angiography room, and the beginning of coronary angiography. Angiography will not begin before confirmation of PRU. Patients who exhibit HPR defined as a PRU value of 240 units or more by VerifyNow (Accumetrics, San Diego, CA, USA) will be randomized and followed by assignment to either the clopidogrel reloading group (clopidogrel 300 mg) or the prasugrel reloading group (prasugrel 20 mg). Angiography in patients with HPR will begin after administration of the study drug. PR will be checked serially using the VerifyNow (Accumetrics, San Diego, CA, USA) assay at four hours, 24 hours and 30 days after PCI. Patients will be required to visit the outpatient clinic at Day 30 for measurement of PR. For patients discharged before Day 8, a secondary visit at Day 15 will be recommended.

In the clopidogrel reloading group, 300 mg clopidogrel will be reloaded, followed by MDs of clopidogrel 75 mg/day for 30 days. In the prasugrel reloading group, 20 mg of prasugrel will be reloaded, followed by prasugrel administration of 5 mg/day for 30 days.

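### The 55% and 70% inhibition inputs do not describe the patients randomised, so the stated 80% power is not supported for HPR at 24 hours

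*Protocol article*

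**What the plan says.** All planning figures are in the Sample size section of the protocol article. The aim is "to detect a 15% difference in PR suppression between reloading with prasugrel and clopidogrel", "to a power of 80% to demonstrate difference", at a two-sided 5% level with a Student's t test. The section says the calculation rests on the primary outcome.

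- Control input: "we assume the inhibition of PR after a LD of clopidogrel to be approximately 55% of baseline", credited to previous reports.
- Experimental input: "The assumed inhibition of PR after LD of prasugrel is 70" per cent. It is said to have been calculated from a 30% higher active-metabolite concentration in East Asians and "an approximate 90% inhibition of baseline PRU two hours after a prasugrel 30 mg LD was given in healthy Korean people". The calculation is not shown. The only link to the trial's patients is an expectation that the difference will be at least 15% in ACS.
- Result: 38 per group after allowing for 20% loss, 76 in total. No SD is given.
- Screening: "We predict that 50% of patients will exhibit HPR as determined by VerifyNow" after the clopidogrel load, hence 152 screened.

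The Intervention and comparator descriptions section defines who is randomised: "Patients who exhibit HPR defined as a PRU value of 240 units or more by VerifyNow". That PRU is read in the angiography room, after the clopidogrel load. Later readings are at 4 hours, 24 hours and 30 days. Reloading is with clopidogrel 300 mg or prasugrel 20 mg. Under Measurement of outcomes, the primary endpoint is HPR (240 units or more) at 24 hours after PCI.

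**The concern.** The design selects patients for a poor response to a clopidogrel load, then sizes the trial on the response to a clopidogrel load in general. The 55% thus describes a group from which the trial takes only the unresponsive part. It is also a change from a baseline for which the trial schedules no reading. If baseline is instead taken as the post-load PRU, a first-load response is being applied to treated patients already shown to respond poorly.

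The 70% has the same weakness: its main source differs from the trial in population, dose and reading time.

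The 15-point difference drives the sample size. If it does not apply to the enrolled patients, neither does the 80%. Taken at face value from an entry PRU not far above 240, 55% and 70% would bring nearly everyone in both arms below the threshold and leave the primary endpoint with few events.

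**Working it through.** **1. The plan's own figures.** 70 − 55 = 15 points, and 76 / 0.50 = 152; both hold. The 38 per group can only be solved backwards, because no SD is stated. A two-sided 5% t test with 80% power and 30 per arm needs a standardised difference of 0.7356, so SD = 15 / 0.7356 = 20.4 points. Then 30 / 0.8 = 37.5, rounded up to 38. The figure is attainable with an SD of about 20.4, which is used below as an assumption.

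**2. Sources against trial.**

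| | Source of the 55% | Source of the 90% | Trial |
|---|---|---|---|
| Patients | response to a clopidogrel load; no selection on HPR stated | healthy Koreans | Korean centre, ACS, PRU ≥ 240 after loading |
| Dose | clopidogrel load, dose not stated in the section | prasugrel 30 mg | reload: clopidogrel 300 mg or prasugrel 20 mg |
| Time | not stated | 2 hours | 24 hours after PCI |
| Baseline | not defined | baseline PRU | first PRU is after the clopidogrel load |

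**3. Where 70% could come from.** 90 / 1.3 = 69.2 and 55 × 1.3 = 71.5 both land near 70, but neither route is stated. The first divides a Korean result by an East Asian exposure factor that the result already contains.

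**4. 55% inhibition beside 50% HPR.** With a symmetric distribution, half the patients are at 240 or more when typical post-load PRU is 240. At 55% inhibition this needs a pre-drug PRU of 240 / 0.45 = 533. The documents give no pre-drug PRU. For an assumed value B, P(HPR) = Φ{[(1 − 240/B) × 100 − 55] / SD}:

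| B | SD 20.4 | SD 30 |
|---|---|---|
| 300 | 4% | 12% |
| 350 | 12% | 22% |
| 400 | 23% | 31% |
| 500 | 44% | 46% |

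**5. What 55% and 70% imply for the primary endpoint.** Apply them to a common post-load entry PRU E, with normal inhibition and SD 20.4. HPR at 24 hours is Φ{[(1 − 240/E) × 100 − m] / 20.4}, with m = 55 or 70. Example at E = 300: (20 − 55)/20.4 = −1.716 gives 4.3%, and (20 − 70)/20.4 = −2.451 gives 0.7%. Power is the exact binomial probability that the uncorrected chi-square test gives P < 0.05.

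| Entry PRU | HPR, clopidogrel | HPR, prasugrel | Power, 30 per arm | Power, 38 per arm |
|---|---|---|---|---|
| 280 | 2.3% | 0.3% | 0.4% | 1.0% |
| 300 | 4.3% | 0.7% | 3.2% | 6.2% |
| 320 | 7.1% | 1.4% | 11.0% | 18.2% |
| 350 | 12.4% | 2.9% | 27.7% | 37.1% |

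Expected events among all 76 patients run from 38 × (0.023 + 0.003) ≈ 1 to 38 × (0.124 + 0.029) ≈ 6. Searching over all common entry values, power peaks at about 62% (30 per arm) and 72% (38 per arm). The peak lies near an entry PRU of 640, where the HPR proportions are 64% and 36%.

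**6. Sensitivity on the t-test scale.** With SD 20.4 and 30 per arm, power is 80% for 15 points and 46% for 10 points.

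**The case against.** The strongest reply is that nothing here is an arithmetic error and that several tempting conclusions go too far. Much of that stands.

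- A reader might infer that 55% inhibition and 50% HPR cannot both be true. The documents do not show this. They give neither a pre-drug PRU nor a spread, and the two figures may come from different populations, doses or times. The 533 is a condition for agreement, which the text neither gives nor rules out.
- A reader might say that 70% does not follow from the cited figures. It can be reached from them. The fault is that the route is not shown and the sources fit poorly. A lower dose and sicker patients are also possible reasons to assume less than 90%.
- A reader might scale 90% in proportion to dose (90 × 20/30 = 60%) and claim a 5-point effect. The same line gives 30% at 10 mg, yet the Discussion reports that a 10 mg prasugrel loading regimen acted much like a 300 mg clopidogrel one, and the plan puts a clopidogrel load at about 55%.
- A reader might call 152 wrong, or predict how few patients it would yield. It follows from the stated 50%. Any yield depends on an assumed pre-drug PRU, and more screening would change neither the 76 nor the power.

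Two further replies have partial force. Step 5 takes baseline to be the post-load PRU, whereas the sources may mean a pre-drug value. That is so, but the post-load PRU is the only pre-reload reading this trial schedules. The chi-square result also overlaps with the separate matter of sizing a binary endpoint on a continuous measure, and should not be counted twice. The mismatch in step 2 needs no assumption and is untouched. Nor does condensation into an article excuse it, since these inputs are stated and relied on.

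**Conclusion.** The point holds as a mismatch of inputs, not as a proven contradiction. From the documents alone, the 55% is not the response of patients selected for HPR after loading. Inhibition from a pre-drug baseline cannot be computed from the scheduled readings. The 70% rests on another population, dose and time, with an ethnic adjustment that has no clear role. The 15-point effect is therefore weakly supported for these patients, and the 80% is not established for HPR at 24 hours.

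The size depends on assumptions: SD about 20.4 points, normal inhibition, and one entry PRU common to all patients. At 280 to 350, power is about 0.4–28% with 30 per arm and 1–37% with 38, and no common entry value brings it to 80%. The tension between 55% and 50% HPR is a secondary sign that the inputs were not checked against each other. It bears on the screening forecast, not on power.

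**What to change.** Keep 76 randomised and rewrite the Sample size section:

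1. Replace 55% and 70% with the assumed 24-hour PRU mean and SD, and the HPR proportion, in each arm for patients at 240 PRU or more after loading. Express any inhibition from the post-load PRU.
2. Drop the ethnic scaling of a result already obtained in Koreans, and show how the prasugrel assumption is reached.
3. State power for HPR at 24 hours as a range over those assumptions, at 30 and at 38 per arm, in place of a single 80%.
4. Describe 152 screened as a forecast that depends on the 50% HPR rate, and give the source of that rate.

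This is rewording, with no change to treatment, visits or sample size. The cost is that the stated power becomes a range, and a less favourable one.

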### Measurement of outcomes

The primary endpoint of this study will be HPR at 24 hours after PCI, as determined by the VerifyNow (Accumetrics, San Diego, CA, USA) assay during the study period (Table 2). The optimal cutoff value is defined as 240 units, as observed by Marcucci *et al*. [9]. Secondary endpoints include major adverse cardiovascular events at 30 days after PCI, including death from cardiovascular cause, myocardial infarction (MI), stent thrombosis, hemorrhagic or non-hemorrhagic stroke, and bleeding events defined by Thrombolysis in Myocardial Infarction (TIMI), as well as Bleeding Academic Research Consortium (BARC) criteria. HPR at four hours or 30 days after PCI will also be evaluated.

**Table 2 T2:** Primary and secondary outcomes

**Primary outcome**	**Secondary outcomes**
HPR (PR ≥ 240 units)	Death from cardiovascular cause
	Myocardial infarction
	Stent thrombosis
	Hemorrhagic or non-hemorrhagic stroke
	Target vessel revascularization
	Bleeding event defined by Thrombolysis in Myocardial Infarction (TIMI) criteria and BARC

HPR, high platelet reactivity: more than 240 units determined via VerifyNow (Accumetrics, San Diego, CA, USA); PR, platelet reactivity; BARC, bleeding academic research consortium.

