### Statistical analysis

The focus of this trial is to compare the efficacy and safety between both study groups. The statistical analyses will be performed on the full analysis set, which will include data from all randomized patients receiving at least one dose of study medication. The safety analysis will include calculation of frequencies, rates of complications, and occurrence of any serious adverse events reported in the two groups.

Descriptive statistics will be calculated according to the scale level of the variables. Continuous data will be analyzed using Student’s *t* test. The chi-square test will be used for categorical variables. A value of *P* < 0.05 will be used to denote statistical significance.

The effect of treatment will be expressed as relative risk estimates and absolute risk reduction. The primary outcome will be analyzed using multivariate logistic regression, adjusting for clinically relevant baseline imbalances. The remaining secondary outcomes will be analyzed using simple 2 × 2 tables and logistic regression. In all analyses, statistical uncertainty will be quantified via 95% confidence intervals. All statistical data will be analyzed using SPSS Version 12.0 (SPCC Inc., Chicago, IL, USA).

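### The 80% power is calculated for a t test on mean platelet inhibition and is not shown for the binary primary endpoint, HPR at 24 hours

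*Protocol article*

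**What the plan says.** Three sections of the protocol article bear on this point.

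- **Measurement of outcomes:** "The primary endpoint of this study will be HPR at 24 hours after PCI". On the threshold: "The optimal cutoff value is defined as 240 units". Each patient is therefore counted as having HPR or not, and Table 2 agrees.
- **Statistical analysis:** "The primary outcome will be analyzed using multivariate logistic regression, adjusting for clinically relevant baseline imbalances". Treatment effects are to be given as relative risks and absolute risk reductions.
- **Sample size:** "The sample size calculation is based on the primary outcome and the primary analysis for the intention-to-treat population". The same paragraph assumes mean inhibition of 55% with clopidogrel and 70% with prasugrel, 80% power, two-sided α of 5%, 20% loss to follow-up and a two-sided Student's t test, "which determined that 38 patients in each group would be required to detect this difference".

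The only HPR rate in the article is the 50% predicted after the initial clopidogrel load. That figure sets the number to be screened (152 for 76 randomised). Under Intervention and comparator descriptions, every randomised patient has HPR at entry, so it says nothing about HPR in either arm at 24 hours.

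Trial objectives words the primary aim as a comparison of platelet reactivity, which is closer to the variable that was sized than to the endpoint that was named.

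**The concern.** A t test on mean percent inhibition is neither the primary outcome nor the primary analysis. The sentence giving the basis of the sample size is therefore wrong as written, and nothing elsewhere in the article repairs it.

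The power of a comparison of means does not carry over to a comparison of proportions above a threshold. Dichotomising discards information, and how much depends on where the threshold falls in each arm's distribution. The article gives no 24-hour HPR rates from which to judge this.

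The practical risk is in reporting. A non-significant HPR result would be presented as coming from a trial with 80% power, and the document does not support that statement for HPR.

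**Working it through.** **Inputs from the Sample size section:** means 55% and 70% (difference 15 points), two-sided α = 0.05, power 0.80, loss 20%, 38 per arm. The SD is not stated. That alone is not held against a condensed article, but it means the SD has to be back-solved.

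**1. Reproducing 38 per arm as a t-test size.**
n = 2(1.960 + 0.842)² × SD² / 15². With SD = 20.5, n = 29.3, rounded up to 30. Allowing for loss, 30 / 0.8 = 37.5, rounded up to 38. The plan's figure is reproduced, given that SD.
Working back, 38 × 0.8 = 30.4, so about 30 per arm. With the noncentral t distribution, 80% power at 30 per arm needs a standardised difference d = 0.736, so SD = 15 / 0.736 = 20.4 points.

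**2. Could 38 be a two-proportion size?**
Reading 55% and 70% as proportions, with the usual pooled-variance formula, gives 163 per arm before loss and 163 / 0.8 = 204 after. So 38 is not a two-proportion size.

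**3. Carrying the sized effect over to a binary endpoint.**
Assume inhibition is normal with equal SD in both arms. HPR means inhibition below some cut c. Then p_C = Φ((c − 55)/SD) and p_P = Φ((c − 70)/SD) = Φ(Φ⁻¹(p_C) − d), with d = 0.736. Power is the exact binomial power of the two-sided uncorrected chi-square test, standing in for the treatment term of a logistic model without covariates.

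| Assumed control HPR | Implied prasugrel HPR | Power, 30 per arm | Power, 38 per arm |
|---|---|---|---|
| 20% | 5.7% | 40% | 49% |
| 30% | 10.4% | 48% | 59% |
| 40% | 16.1% | 55% | 66% |
| 50% | 23.1% | 58% | 69% |
| 60% | 31.5% | 62% | 72% |
| 64% | 35.3% | 62% | 72% |
| 70% | 41.6% | 61% | 71% |
| 80% | 54.2% | 57% | 68% |

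The maximum lies near the symmetric cut (64% against 35%). No row reaches 80%, even with all 38 per arm evaluable.

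**4. HPR difference that would have 80% power** (normal approximation, assumed control rates).

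| Control HPR | Prasugrel HPR needed, 30 per arm | Difference | Prasugrel HPR needed, 38 per arm | Difference |
|---|---|---|---|---|
| 40% | 9.4% | 31 points | 12.2% | 28 points |
| 50% | 16.6% | 33 points | 19.8% | 30 points |
| 60% | 24.9% | 35 points | 28.6% | 31 points |

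**5. Assumed rates on either side of 80%** (exact power, 30 / 38 per arm): 30% against 10%, 50% / 61%; 50% against 20%, 69% / 80%; 50% against 15%, 85% / 92%; 60% against 20%, 91% / 96%.

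**The case against.** The strongest objection is that the power for HPR is unknown rather than known to be low. The article states no 24-hour HPR rates, and rates such as 50% against 15% would give more than 80%. That stands. A reader might infer that the trial is underpowered, and the documents do not establish it.

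Three further inferences are tempting and should not be drawn:

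- **That the trial has only about 22% power.** This figure belongs to a 15-point difference in HPR rate (45% against 30%, 30 per arm). The 15 points in the plan are a difference in mean inhibition. The plan never posits a 15-point difference in HPR.
- **That the endpoint will have almost no events.** This follows only if 55% and 70% inhibition are applied to the PRU measured after the clopidogrel load (for example 300 falling to 135 or 90). The article does not say which baseline is meant, and it may be the value before any thienopyridine.
- **That about 60 patients will be evaluable at 24 hours.** The 20% is a general follow-up loss rate, and follow-up runs to day 30. The sentence "A total of 76 patients will be randomized and included in the analysis" can be read as an intention-to-treat statement. Both 30 and 38 per arm are shown above for this reason.

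It is also fair that the sized comparison matches the wording of the primary aim, and that 95% confidence intervals are promised throughout, so a null HPR result would not be uninterpretable. Neither removes the contradiction between the stated basis of the sample size and the named endpoint and analysis.

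**Conclusion.** The concern holds as a mismatch. The 80% power belongs to a t test on mean inhibition, the article attributes it to the primary outcome and primary analysis, and it is not shown for HPR at 24 hours.

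On the effect actually sized, the corresponding power for a dichotomised endpoint is about 40 to 62% with 30 per arm and 49 to 72% with 38. This rests on normality, a common SD of about 20 points back-solved from 38 per arm, control HPR between 20 and 80%, and an unadjusted chi-square test in place of the adjusted logistic model. Power would reach 80% only with an HPR difference larger than that effect implies, about 31 to 35 points with 30 per arm or 28 to 31 with 38, for control rates of 40 to 60%. Whether such a difference is realistic cannot be judged from the article.

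**What to change.** In the Sample size section:

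1. Withdraw the statement that the calculation rests on the primary outcome and primary analysis. Attribute the 80% power to the t test on inhibition of platelet reactivity.
2. State the assumed 24-hour HPR rate in each arm. Report the resulting power, or the detectable difference, for the HPR comparison with all 38 per arm and with 30 per arm (38 less the 20% loss).

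In the Statistical analysis section:

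3. Pre-specify the comparison of platelet reactivity at 24 hours, adjusted for pre-randomisation PRU, as a key supporting analysis. It matches the aim in Trial objectives and is close to the variable that was sized.

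HPR can remain primary. Exchanging the primary endpoint would be a material change in an open-label trial that has been randomising since November 2012, and correcting the power statement does not require it.

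The cost is an amendment to the text. No extra patients, visits or assays are needed, since platelet reactivity is already measured before PCI and at 24 hours. The downside is a power statement that is probably less favourable than the present one.
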